3	Alternative composite threshold: ≥100 m absolute MWD gain	Tests sensitivity to an absolute rather than relative distance criterion
4	Functional improvement component only (no revascularization criterion)	Isolates the predictive relationship with functional adaptation. Mandatory pre-specified secondary analysis; reported in all primary publications regardless of composite outcome result.
5	Revascularisation-free survival component only	Isolates the predictive relationship with intervention requirement. Mandatory pre-specified secondary analysis; reported in all primary publications regardless of composite outcome result.
6	Restriction to guideline-concordant revascularisation events only	Removes patient-preference-driven events to reduce confounding; specifically examines discordant cases (functional improvement achieved but revascularisation occurred)
7a	Four-predictor model: muscle density, VAT, age, sex (excluding baseline MWD)	Robustness check with an EPV approximately 10; tests stability of primary model estimates when baseline MWD is excluded
7b	Three-predictor model (muscle density, VAT, age; excluding sex)	Robustness check with an EPV approximately 13–14
8	Alternative muscle density threshold: 33 HU	Tests lower threshold sensitivity for myosteatosis classification (Martin et al. [21] value for BMI ≥ 25 kg/m^2^); see also Section 2.6
9	Alternative muscle density threshold: 41 HU [Martin et al. [21], BMI < 25 kg/m^2^ stratum]	Tests higher threshold sensitivity for myosteatosis classification; see Section 2.6
10	Alternative VAT threshold: --20 cm^2^ (110 cm^2^ M; 80 cm^2^ F)**†**	Tests sensitivity to a more conservative VAT threshold
11	Alternative VAT threshold: +20 cm^2^ (150 cm^2^ M; 120 cm^2^ F)**†**	Tests sensitivity to a more stringent VAT threshold
12	Adherent subgroup (≥30/36 sessions completed)	Per-protocol analysis to assess treatment-specific effects
13	30% treatment failure rate scenario (approximately 30 failures)	Reports model performance and power under a more optimistic clinical assumption
14	Expanded confounding model: primary five predictors plus ABI, smoking status, diabetes, Clinical Frailty Scale score, TASC II classification, SMI, SAT	Pre-specified secondary expanded model; EPV approximately 3–4 (acknowledged limitation); designated as robustness sensitivity analysis; tests whether primary predictor associations are independent of additional clinical confounders

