The composite endpoint comprises four pre-specified outcome combinations, addressed as follows: The primary analysis of treatment failure includes three specific scenarios: (i) program non-completion, defined as failure to attend the requisite number of SET sessions, regardless of functional outcome; (ii) functional non-response among program completers, characterized by completion of the program without achieving the MWD threshold at three months (T1); and (iii) revascularization occurring within the three-month follow-up period, irrespective of functional outcome. This approach aligns with the protocol’s objective of identifying patients capable of deriving sufficient benefit from conservative management alone. The rationale for classifying revascularization as treatment failure, even when accompanied by functional improvement, is that such cases indicate the conservative management pathway was not maintained. Sensitivity analysis #6 (Table 3) examines the subset of guideline-concordant revascularization events separately.

The four pre-specified outcome combinations are: (1) functional improvement achieved AND revascularization-free = treatment success; (2) functional improvement not achieved AND revascularization occurred = treatment failure; (3) functional improvement achieved BUT revascularization occurred = classified as treatment failure in the primary analysis; this discordant case type (functional improvement with revascularization) will be specifically examined in sensitivity analysis #6 (Table 3), restricting to guideline-concordant revascularization events only, to assess whether revascularization was guideline-concordant or driven by patient preference; (4) functional improvement not achieved AND revascularization-free = treatment failure. Failure to meet either criterion (b) or the MWD threshold in (a) constitutes treatment failure.

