### Secondary and exploratory outcomes

Secondary outcomes, evaluated at baseline (T0) and three months (T1), include: standardized treadmill MWD and PFWD; absolute and relative change in MWD from baseline to T1 (continuous secondary outcomes); 30-second chair stand test repetitions; bilateral handgrip dynamometry (kg); 2-minute walk test distance; and Walking Impairment Questionnaire (WIQ) domain scores. Exploratory outcomes assessed at 6, 12, and 18 months—such as late revascularization, MALE, MACE, and all-cause mortality—are obtained through structured telephone follow-up, medical records review, and registry linkage. Given the anticipated low event counts during extended follow-up in this cohort, exploratory outcomes will be reported descriptively and interpreted as hypothesis-generating only.

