**Multiple imputation specification**: Missing data are addressed through multiple imputation by chained equations (MICE). All analysis variables—including the primary composite outcome, all five primary predictors, all covariates in the expanded model, and secondary outcomes—are incorporated into the MICE model. Twenty imputation datasets are generated (50 iterations per dataset), and estimates are pooled according to Rubin’s rules. Imputation diagnostics include convergence trace plots and comparisons of observed versus imputed variable distributions. A complete-case sensitivity analysis is pre-specified (Table 3, sensitivity analysis #15). For follow-up data potentially deviating from the missing-at-random assumption, pattern-mixture models and tipping-point analyses are pre-specified.

Cumulative incidence functions are reported alongside cause-specific hazard analyses. Pre-specified sensitivity analyses are detailed in Table 3. Component-separate analyses of the functional improvement component (excluding the revascularization criterion) and the revascularization-free survival component are designated as mandatory pre-specified secondary analyses (Table 3), not optional sensitivity analyses; these analyses isolate each failure mode and will be reported in the primary publication regardless of the primary composite outcome results.

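### As defined, mandatory analysis #4 and the walking-distance change outcomes take the T1 treadmill result even when a revascularisation came before it, so they do not isolate the response to SET

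*Protocol article*

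**What the plan says.** - **Functional criterion** (Primary outcome): a treadmill gain in maximum walking distance (MWD) of at least 50 m or 50% from baseline, assessed at three months (T1).
- **Revascularisation** (Primary outcome): one failure scenario is "revascularization occurring within the three-month follow-up period, irrespective of functional outcome". The third of the four outcome combinations reads "functional improvement achieved BUT revascularization occurred = classified as treatment failure in the primary analysis".
- **Non-completion** (Primary outcome): a separate failure scenario is "program non-completion, defined as failure to attend the requisite number of SET sessions, regardless of functional outcome".
- **Analysis #4** (Table 3): the functional component alone, with the revascularisation criterion dropped. The rationale given is that it "Isolates the predictive relationship with functional adaptation".
- **Status of the component analyses** (Statistical analysis): "these analyses isolate each failure mode and will be reported in the primary publication regardless of the primary composite outcome results".
- **Continuous outcomes** (Secondary and exploratory outcomes): absolute and relative MWD change from T0 to T1, and pain-free walking distance (PFWD) at both times. No rule is given for revascularised patients.
- **Treadmill tests** (Table 4): T0, T1, and a withdrawal visit for people who leave the study. None is tied to a procedure.

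**The concern.** In the composite it does not matter when the T1 test falls relative to a procedure, because revascularisation is failure anyway. Analysis #4 removes that safeguard and keeps the T1 value. If the procedure came first, #4 credits SET with a walking gain that the procedure may have produced. The error runs mainly one way: patients in whom SET did not work are relabelled as responders.

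The same value enters the MWD and PFWD changes and the Spearman correlations built on them. Outcome combination (3) likewise cannot separate improvement from exercise from improvement after a procedure.

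Analysis #4 has to be reported whatever the composite shows. Readers would take it as the direct test of whether body composition predicts adaptation to exercise, which is the study's biological premise. An association pulled towards no effect there could be misread as evidence against that premise.

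**Working it through.** **1. Tracing the definitions.** Take a patient revascularised before T1 whose T1 distance is at least 50 m or 50% above baseline.

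| Analysis | Rule applied | Result |
|---|---|---|
| Primary composite | revascularisation is failure | failure |
| #4, non-completion rule dropped | T1 gain only | success |
| #4, non-completion rule kept | T1 gain and enough sessions | success only if enough sessions were attended |
| MWD/PFWD change | T1 minus T0 | positive change |

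The Discussion describes the second failure mode as progression to revascularisation before the programme is complete, so procedures before T1 are expected. Analysis #6 sorts procedures by guideline concordance and does not alter the MWD value.

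**2. The non-completion rule.** At three sessions a week, week 6 gives 3 × 6 = 18 sessions. If the required number is the 30 of 36 that the SET section calls adequate adherence, it is first reached at 30 / 3 = 10 weeks. With the rule kept, only patients revascularised from about week 10 up to T1, or who returned and made up sessions, can leak into #4. The article does not say whether the rule applies in #4. It gives the continuous outcomes no protection.

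**3. Figures available.** No stated figure measures this effect. The sample-size frame is 128 × 0.78 = 99.84, about 100 evaluable patients, and 40 / 5 = 8 events per variable. The 40% failure rate includes early revascularisation without giving its share.

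**4. Illustration A, upper end (all inputs assumed).** n = 100, 1,000 replicates per scenario. True non-response is 30%, with logit P(non-response) = a + ln(2) × z, where z is the predictor in SD units. All revascularised patients are true non-responders and all pass at T1. Figures are the median odds ratio (OR) per SD and, where shown, power at two-sided 0.05 (82–84% before recoding in the random scenarios).

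| Revascularised | Random among non-responders | Also rising with the predictor (OR 2 per SD) |
|---|---|---|
| 2% | 1.97–1.99 | 1.82–1.83 |
| 5% | about 1.9, power 71% | about 1.6, power 48% |
| 10% | about 1.8, power 56% | about 1.3, power 17% |

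**5. Illustration B, milder (all inputs assumed).** True non-response is 25%, revascularisation is four times likelier in non-responders, and 80–95% pass afterwards. With overall rate r, the rate in responders is r / (0.25 × 4 + 0.75) = r / 1.75. At r = 5% this is 2.86%, and 11.43% in non-responders. True non-responders relabelled per 100 are 25 × 0.1143 × 0.80 = 2.3 to 25 × 0.1143 × 0.95 = 2.7.

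| Revascularised | OR in #4 (true 2.00) | Relabelled per 100 |
|---|---|---|
| 3% | 1.96 | 1.4–1.6 |
| 5% | 1.92–1.93 | 2.3–2.7 |
| 10% | 1.84–1.87 | 4.6–5.4 |
| 15% | 1.77–1.81 | 6.8–8.1 |

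**6. Would imputation repair it?** At 5% under the assumptions of A, setting the post-procedure values to missing and imputing under missing at random (MAR) moves the OR from 1.87 to 1.99 when revascularisation is random among non-responders. When it also tracks the predictor, the OR moves only from 1.58 to 1.79. That is half the loss: (1.79 − 1.58) / (2.00 − 1.58) = 0.50.

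**The case against.** **This is detail for the analysis plan.** The article condenses a fuller plan, and no sentence says post-procedure tests will be used. That is inferred from the time windows and the absence of another rule, and a T1 test could precede a late procedure. This stands as a limit on certainty. It does not rescue the text, because the article fixes the definition of #4 and states what the analysis achieves, and the definition does not support the statement.

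**The effect may be tiny.** The Introduction cites 25% revascularised over five years among conservatively managed patients. Spread evenly over 20 quarters (an assumption), that is 25 / 20 = 1.25% per quarter, or 1 to 2 patients among 100–128. Concordant events require at least 12 weeks of SET, so they fall close to T1. This largely stands, although events may cluster early and a cohort selected by CTA work-up may run higher.

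**Using T1 regardless is a legitimate treatment-policy choice.** It is, and it fits the intention-to-treat wording. It answers how far patients walk after a strategy that may include a procedure, which is a different question from adaptation to exercise.

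**Stronger readings that the documents do not support.** A reader might infer that the primary result is biased. It is not, because revascularisation is already failure there. A reader might infer that anyone revascularised mid-programme becomes a success in #4. That depends on the unsettled non-completion rule. A reader might infer severe attenuation, to an OR of about 1.3. That needs 10% revascularised within three months, which is one third of the assumed 30% non-responders. It also needs every one to be a true non-responder, every one to pass afterwards, and selection that follows the CT predictor.

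**Conclusion.** The point holds for #4 and for the MWD/PFWD change outcomes. On the stated definitions, procedure benefit can be scored as SET adaptation, and the claim that #4 isolates functional adaptation is not supported. H1 and H2, which rest on the composite, are untouched.

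The size cannot be fixed from the documents. It rests on an assumed revascularisation rate, an assumed true OR of 2.0 per SD and assumed post-procedure success. With one or two events per 100 the loss is small. At 5–10% it is moderate, and it is large only in the extreme case. All binary figures shrink if non-completion remains a failure in #4, while the continuous outcomes stay exposed. The change should be made before enrolment starts, but the study's main conclusion does not depend on it.

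**What to change.** 1. In #4 and all analyses of MWD or PFWD change, do not use treadmill tests done after a lower-limb revascularisation.
2. Use a test done after baseline and before the procedure if one exists. Do not carry T0 forward, since that forces zero change and scores the patient as a failure. Otherwise set the T1 value to missing and impute it with the planned MICE model.
3. MAR imputation may be too optimistic for these patients, so apply to them the tipping-point analysis that the Statistical analysis section already plans. Scoring all of them as non-responders, as the composite does, is one bound. The T1 values as observed are the other.
4. State whether programme non-completion remains a failure in #4, and that combination (3) refers to improvement shown before the procedure.
5. Report how many T1 tests followed a procedure, and replace the wording that #4 isolates functional adaptation.

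The cost is wording, a few more imputed values and one more bounded analysis. Sample size, the primary analysis and patient care do not change.

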## Introduction

Peripheral arterial disease (PAD) affects approximately 236 million individuals aged 25 years and older, with intermittent claudication being its most common symptomatic manifestation [1]. International clinical practice guidelines, including the 2024 American College of Cardiology/American Heart Association (ACC/AHA), 2024 European Society of Cardiology (ESC), and 2024 European Society for Vascular Surgery (ESVS) guidelines, unanimously endorse supervised exercise therapy (SET) as the first-line treatment for intermittent claudication [2–4]. Furthermore, the 2024 ESC and ESVS guidelines specify that revascularization should be deferred until conservative management has been adequately trialed [3, 4]. A Cochrane systematic review demonstrates that exercise significantly enhances maximum walking distance and functional performance compared to no exercise [5]. Additionally, a second Cochrane review confirms the superiority of SET over home-based exercise and walking advice alone [6]. A meta-analysis of 15 randomized controlled trials shows significant improvements in physical health-related quality of life and perceived walking ability with structured exercise programs, although mental health component scores were not significantly affected [7].

Despite these benefits at the population level, individual treatment responses exhibit considerable heterogeneity. In the Invasive Revascularization or Not in Intermittent Claudication (IRONIC) study, 25% of conservatively managed patients ultimately required revascularization over five years, despite achieving comparable long-term outcomes to the revascularization group. This underscores both the tolerability of conservative management and the existence of a subgroup with insufficient response [8]. Real-world SET series report non-completion rates of 40–50% [9]. Conventional clinical predictors — including ankle-brachial index (ABI), age, sex, and disease severity — do not reliably forecast the extent of functional improvement achieved with SET [10]. However, patients with lower baseline walking capacity may derive proportionally greater benefits [10]. Currently, no validated metabolic tool exists to identify, prior to therapy initiation, patients lacking the biological substrate for aerobic adaptation, making them unlikely to benefit from a sustained exercise program.

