Classification thresholds for the primary predictors (skeletal muscle density for H1; VAT area for H2) will be derived prospectively within this cohort and treated as pre-specified study outcomes rather than assumptions. For the binary primary composite outcome, optimal cut-points will be identified by maximizing the Youden index (J = sensitivity + specificity -- 1) using the cutpointr R package; 95% confidence intervals will be obtained via 1000-sample bootstrap resampling. Separate derivations will be conducted for skeletal muscle density (single threshold) and VAT area (sex-stratified: men and women analyzed independently to account for dimorphic adipose tissue distribution). For the secondary time-to-revascularization outcome, optimal cut-points will also be identified by maximizing the log-rank statistic via survminer::surv_cutpoint(), providing a time-to-event-appropriate complement to the Youden-index approach. Each threshold derivation will report the optimal cut-point value, Youden index, sensitivity, specificity, and 95% bootstrap CI. As thresholds will be derived from the same cohort used for evaluation, internal optimism is anticipated and explicitly acknowledged. Thus, all threshold-based classification results will be interpreted within the derivation-cohort framework, with external validation in an independent PAD multicenter cohort as the pre-specified mandatory next step prior to clinical translation. Literature-derived thresholds from non-PAD populations will be retained as pre-specified sensitivity analyses (Table 3) to facilitate transparent cross-referencing with existing oncological and metabolic literature.

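### The mandatory 3-month revascularisation-only analysis (#5) cannot measure need for intervention, and the plan contradicts itself on the later time-to-revascularisation outcome

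*Protocol article*

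**What the plan says.** Analysis #5 in Table 3 is titled "Revascularisation-free survival component only", and its rationale reads "Isolates the predictive relationship with intervention requirement". With #4 it is a mandatory secondary analysis. Statistical analysis adds that "these analyses isolate each failure mode and will be reported in the primary publication regardless of the primary composite outcome results".

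The row prints no time horizon. The composite is set at three months in Primary outcome and assessed at T1 in Table 4, and the matching failure mode is "revascularization occurring within the three-month follow-up period, irrespective of functional outcome".

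On timing, the Introduction reports that guidelines say "revascularization should be deferred until conservative management has been adequately trialed". The SET section sets a 12-week course. Primary outcome calls an event guideline-concordant only if, among other conditions, an adequate exercise trial of at least 12 weeks has failed.

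On later events, Secondary and exploratory outcomes places late revascularisation at 6, 12 and 18 months among the exploratory outcomes. Expecting low event counts, it says that "exploratory outcomes will be reported descriptively and interpreted as hypothesis-generating only". Yet Statistical analysis states: "For the secondary time-to-revascularization outcome, optimal cut-points will also be identified by maximizing the log-rank statistic". That section also plans cumulative incidence functions and cause-specific hazards, and the Discussion plans a Fine–Gray model.

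**The concern.** There are two problems.

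- **Purpose against window.** If procedures are deferred until conservative care has been tried, a need for intervention caused by failed exercise therapy among programme completers will normally be acted on after T1. What falls inside the window is mostly early departure from the conservative pathway. The result must nevertheless be published under a rationale about intervention requirement. A null or unstable estimate from a handful of events could then be read as evidence on whether CT body composition predicts that need.
- **Status of the time-to-event outcome.** One section calls it secondary and gives it hazard models and an optimised cut-point. Another omits it from the secondary outcomes and limits late revascularisation to description because events will be few. Both cannot hold. Maximising a log-rank statistic over candidate cut-points is especially unstable when there are few events.

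**Working it through.** **The plan's own figures (Sample size).** 100 / (1 − 0.22) = 128.2 and 128 × 0.78 = 99.8, so 128 enrolled and 100 evaluable agree within rounding. 100 × 0.40 = 40 failures, and 40 / 5 = 8 events per variable. No event count is given for #5. Early revascularisation sits inside the 40% and is not split out.

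**Window.** Three months is 365.25 / 4 = 91 days. The course takes 12 × 7 = 84 days. If it starts at T0 and runs to schedule, about 7 days remain in which an event could follow a full 12-week trial. Almost any in-window event would therefore fail the protocol's own definition of guideline-concordant. This step needs no event rate.

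**Expected events at three months.** The only revascularisation rate in the article is "25% of conservatively managed patients ultimately required revascularization over five years", from the conservative arm of a cited trial.

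- Linear scaling: 0.25 × 0.25 / 5 = 1.25%, or 1.3 of 100 and 1.6 of 128.
- Constant hazard: h = −ln(0.75) / 5 = 0.0575 per year, and 1 − exp(−0.25h) = 1.43%, or 1.4 of 100 and 1.8 of 128.
- Chance of no event at all: 0.75^(0.05 × 100) = 0.24 for 100 patients, and 0.75^(0.05 × 128) = 0.16 for 128.

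**Range if early risk is higher (assumed).**

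| Assumption | 3-month risk | Events of 100 | Events of 128 |
|---|---|---|---|
| Constant hazard | 1.43% | 1.4 | 1.8 |
| Early hazard × 2 | 2.84% | 2.8 | 3.6 |
| Early hazard × 3 | 4.22% | 4.2 | 5.4 |
| Early hazard × 5 | 6.94% | 6.9 | 8.9 |
| One third of the 25% within 3 months | 8.33% | 8.3 | 10.7 |

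If the five primary predictors were used, events per variable would run from 1.4 / 5 = 0.3 to 10.7 / 5 = 2.1. The protocol calls 8 modest and flags 3 to 4 as a limitation for #14. It flags nothing for #5.

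**Same scaling at 18 months.** Linear: 0.25 × 1.5 / 5 = 7.5%, or 7.5 of 100 and 9.6 of 128. Constant hazard: 1 − exp(−1.5h) = 8.27%, or 8.3 of 100 and 10.6 of 128. Under a constant hazard that is about six times the 3-month count, but still only 8.3 / 5 = 1.7 to 10.6 / 5 = 2.1 events per variable with five predictors.

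**Rough power for one predictor** at an odds ratio of 2 per SD (an illustrative effect), Φ(ln 2 × √(np(1 − p)) − 1.96): 0.13 (n = 100) and 0.15 (n = 128) at three months, 0.48 and 0.58 at 18 months. The normal approximation is poor at such counts, so these show order of magnitude only.

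**The case against.** The strongest reply is that in-window revascularisation is exactly what the protocol means to count. The Discussion describes this failure mode as moving to revascularisation before the programme is finished, and Primary outcome explains that the conservative pathway was then not maintained. Reporting each component over the composite's own horizon is good practice, and publishing a sparse component is transparent. This stands, and it is why #5 should stay at three months. It does not rescue the stated rationale, which is about need for intervention.

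Four stronger readings are tempting, and the documents do not support them.

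- **That the protocol itself predicts 1 to 2 events.** It gives no 3-month rate. The 25% comes from another trial, which Sample size says was not designed to quantify non-response to exercise therapy, and the constant hazard is an assumption. This cohort is selected through revascularisation work-up, and patients who leave the programme early may have procedures sooner.
- **That #5 should become an 18-month outcome.** It would then no longer decompose the 3-month composite, and by the same scaling it would still have only about 8 to 11 events.
- **That most 18-month data would be in hand at primary completion in December 2030.** Even accrual would put about 36 / 51 = 71% of patients past 18 months by then, but that is elapsed time. Study design and setting defers assessment of long-term outcomes until after January 2031.
- **That #5 is fixed as a five-predictor model.** No passage sets its covariates, and the unseen analysis plan may do so.

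The word survival in the title of #5 leaves a longer horizon conceivable, but nothing links #5 to one.

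**Conclusion.** The concern holds in a limited form. As a component of the 3-month composite, #5 cannot show whether body composition predicts need for intervention. The window and the protocol's own concordance definition establish that without any rate. The expected count of about 1 to 2 events, 3 to 5 with a two- to three-fold early hazard and 8 to 11 at the extreme, rests on scaling an outside five-year figure. No point in that range supports a multivariable model, and the missing caveat matters because reporting is mandatory.

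The conflict over the time-to-revascularisation outcome is one of stated text and depends on no assumption. The primary analysis of H1 and H2 is unaffected.

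**What to change.** 1. Keep #5 at three months and print that horizon in the row. Report it descriptively: counts by adjudicated class with exact confidence intervals, and at most single-predictor penalised estimates. State the expected sparsity, as is done for #14.
2. Reword its rationale to early abandonment of the conservative pathway.
3. Delete the survminer cut-point derivation for revascularisation.
4. Reconcile Study design and setting, Secondary and exploratory outcomes, Statistical analysis and the Discussion by defining one exploratory outcome, labelled separately from #5: time from T0 to first lower-limb revascularisation through 18 months, with death as competing event. Limit it to cumulative incidence and single-predictor penalised estimates, and report it when the long-term data are available. Add late revascularisation to the follow-up row of Table 4, which now lists only MALE, MACE and mortality.

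The cost is wording, since later revascularisation is already to be collected. The sponsor gives up any multivariable or cut-point result for revascularisation. The 18-month result comes after the primary paper, or earlier with late enrollees censored.
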